## Abstract

**Background:**

Treatment options for knee osteoarthritis (KOA) remain limited. Although previous studies suggest that acupuncture can alleviate pain and functional impairment associated with KOA, there is significant variation in acupoint selection across studies and a lack of objective criteria to guide this choice. Infrared thermography (IRT) is recognized as a reliable method for identifying inflammatory regions in KOA. Our previous research revealed abnormal skin temperature at specific acupoints and surrounding areas in the lower limbs of patients with KOA, indicating potential treatment targets. However, there is still insufficient evidence to support their clinical application.

**Objective:**

This pilot trial aims to assess the feasibility of conducting large-scale studies in the future and to provide preliminary evidence of the effects of acupuncture applied at IRT-guided thermal-sensitized acupoints (TAs) for the treatment of KOA.

**Methods:**

This will be a randomized, controlled pilot trial with participant blinding. A total of 60 patients with KOA will be randomly allocated in a 1:1 ratio to either the TA group or the conventional acupoint group. Both groups will receive 3 acupuncture sessions per week for 4 weeks. In the TA group, acupoint selection will be based on points with abnormal skin temperature identified by IRT using real-time surface projection technology. In the conventional acupoint group, acupoint selection will follow the established prescription validated in previous studies. The primary outcome will be feasibility, assessed using a traffic light system to evaluate recruitment, retention, intervention completion, and completion of other outcome measures. Secondary outcomes will include the visual analog scale for pain, the Western Ontario and McMaster Universities Osteoarthritis Index function subscale, the credibility and expectancy questionnaire, skin temperature, and safety.

**Results:**

The study has been approved by the ethics committee of the Third Affiliated Hospital of Beijing University of Chinese Medicine (BZYSY-2024KYKTPJ-44) and registered in the International Traditional Medicine Clinical Trial Registry. The first participant was enrolled on February 25, 2025, and a total of 30 participants had been enrolled by January 1, 2026. All enrollment and follow-up are expected to be completed by June 2026.

**Conclusions:**

The findings of this study will provide evidence on the feasibility and preliminary clinical effects to support the future adoption of acupuncture prescriptions based on TAs for the treatment of KOA.

**Trial Registration:**

International Traditional Medicine Clinical Trial Registry ITMCTR2025000019; https://itmctr.ccebtcm.org.cn/mgt/project/view/-5870917416012215224

**International Registered Report Identifier (IRRID):**

DERR1-10.2196/81837

## Introduction

Knee osteoarthritis (KOA) is the most prevalent form of osteoarthritis, primarily characterized by chronic pain and functional impairment [1]. Current treatment options remain limited. Although pharmacological therapies may provide short-term symptom relief, their long-term use is often constrained by potential cardiovascular and gastrointestinal risks [2]. Acupuncture is a widely used nonpharmacological intervention and has been proven to be superior to sham acupuncture in certain studies [3,4]. However, these benefits are not consistently observed, particularly in studies conducted outside China [5,6]. Consequently, the American College of Rheumatology and the American Academy of Orthopaedic Surgeons [7,8] have generally assigned acupuncture a limited strength of recommendation in clinical practice guidelines.

The effects of acupuncture can be attributed to both acupoint stimulation and patient expectations [9]. Acupoints are central to acupuncture treatment; however, there is considerable variation in acupoint selection across studies on KOA. Guided by traditional acupuncture theory, more than 40 acupoints have been considered for the treatment of KOA [10,11]. The lack of clear criteria for acupoint selection has raised concerns regarding the adequacy of acupuncture protocols, as most studies fail to provide objective justification for their choice of acupoints [12]. The importance of the many available acupoints in traditional acupuncture theory remains unclear, as meta-analyses have shown no correlation between the number of acupoints used and clinical effect [9]. Experimental studies further support this observation, as animal studies using only 1 to 2 fixed acupoints often conclude that acupuncture is effective [13,14]. One possible explanation is that the effects of acupuncture may not depend on specific acupoints per se but rather on broader subcutaneous tissue stimulation.

Inflammatory diseases are closely related to thermoregulation. The severity of KOA has been shown to correlate with the temperature of specific areas surrounding the knee joint [15,16]. When abnormal temperature changes occur at or near acupoints, it is referred to as acupoint sensitization. These abnormal skin temperature variations may be associated with autonomic nervous system function and metabolic activity, with certain acupoints exhibiting more pronounced temperature changes than nonacupoint regions [17]. Recent anatomical studies [18] have demonstrated a notable overlap between acupoints and perforating cutaneous blood vessels. Using infrared thermography (IRT), it is possible to detect temperature changes in these blood vessels beneath the acupoints [19]. Our previous research [20] indicates that, compared with individuals without KOA, patients with KOA exhibit thermal sensitization at certain acupoints of the lower limbs, showing characteristics of localized and regional thermal consistencies. In the treatment of peripheral facial paralysis, acupuncture intervention at these temperature-abnormal points is effective [21]. However, in the case of KOA, there is currently limited evidence supporting the effectiveness of this acupuncture approach.

Compared with conventional acupoint (CA) selection, thermal-sensitized acupoints (TAs) may offer improved therapeutic effects. Under IRT guidance, these acupoints can be flexibly selected according to individual differences, while the procedure remains easy to standardize. IRT is convenient and noninvasive, which may result in high acceptability without imposing additional burden on participants. Therefore, this study aims to conduct a pilot trial comparing acupuncture using IRT projection technology for acupoint selection with CA therapy for KOA. The goal is to explore the feasibility of conducting a large-scale clinical trial and to assess differences in effectiveness between the two acupoint selection methods in the treatment of KOA.

## Methods

### Study Design

This will be a single-center randomized controlled pilot trial conducted at the Third Affiliated Hospital of Beijing University of Chinese Medicine. Participants will be randomly assigned to the TA group and the CA group in a 1:1 ratio. This study will be reported according to the Standard Protocol Items: Recommendations for Interventional Trials (SPIRIT) guidelines [22] (Multimedia Appendix 1).

### Participants

Before any study-specific procedures are initiated, individuals expressing interest in participation will receive a comprehensive explanation of the study aims, procedures, and relevance. Information regarding potential benefits, risks, and discomforts will be communicated clearly to support informed decision-making. Participation is voluntary, and participants may withdraw at any time. Individuals who decline participation will be informed of available conventional treatment options upon request. Written informed consent will be obtained before eligibility screening.

As this study compared acupuncture applied at TAs with that applied at CAs, the inclusion and exclusion criteria were based on those used in our previous studies evaluating the effects of conventional acupuncture [23]. The inclusion criteria are as follows: (1) age 45 to 75 years, (2) meeting the American College of Rheumatology diagnostic criteria for KOA [24], (3) reporting knee pain for more than 3 months, (4) having undergone radiological examination within the past 6 months indicating a Kellgren-Lawrence grade II or III [25], (5) having a score ≥40 mm in the visual analog scale (VAS) [26] during the past week, and (6) being willing to sign the informed consent.

Patients will be excluded if they meet any of the following conditions: (1) a history of knee joint surgery or plans for knee joint surgery (eg, knee replacement or knee arthroscopy); (2) knee pain attributed to other pathologies (eg, meniscus tear, rheumatoid arthritis, joint cavity infection, malignancy, gout, or lumbosacral disease with symptom of lower extremity); (3) a history of arthroscopy within the past 1 year or intra-articular injection within the past 6 months in the evaluating knee; (4) receipt of acupuncture in either knee within the past 6 months; (5) severe acute or chronic organic diseases or neuropsychiatric disorders; (6) disorders of coagulopathy (eg, hemophilia); (7) presence of a pacemaker or epilepsy; (8) pregnancy, planned pregnancy, or lactation; and (9) participation in other clinical studies within the past 1 month.

### Randomization and Blinding

The randomization sequence will be generated by an independent statistician using Stata (version 17.0; StataCorp). To conceal the contents, opaque envelopes will be used for distribution. These envelopes will be stored and managed by independent researchers not involved in other aspects of the trial. After including participants who met the criteria and obtaining their informed consent forms, random envelopes will be opened sequentially. The acupuncturists will be aware of group assignments, whereas participants and outcome evaluators will remain blinded.

### Interventions

#### Overview

The difference between the two intervention groups will be limited to the selection of acupoints only. All participants will undergo 4 weeks of acupuncture intervention accompanied by electrical stimulation. The treatment will be administered 3 times per week, with each session lasting 30 minutes. Ideally, sessions will be scheduled every other day, and administration of 2 sessions within a 24-hour period will be prohibited. Over a period of 4 weeks, a total of 12 treatments will be provided. Participants will assume a supine position on the treatment bed, and sterile, single-use needles will be used.

After the needle is inserted, the acupuncturists will perform lifting-insertion and twisting-rotating operations for at least 10 seconds to achieve the *deqi* sensation. The electroacupuncture instrument will then be connected, and a sparse-dense wave will be applied. Current intensity will be adjusted according to the participant’s comfort level. The intervention will be delivered by 3 acupuncturists with more than 3 years of clinical experience.

During the trial, participants will be discouraged from undergoing any other treatments that might affect their symptoms, including medications (such as nonsteroidal anti-inflammatory drugs, opioids, etc) and other physical therapies. Participants may use diclofenac sodium enteric–coated tablets (Voltaren, Beijing Novartis Pharma Co., Ltd) for severe pain that cannot be relieved, except within 48 hours before any assessment. If rescue medication is required, participants will receive up to 6 tablets, take 1 tablet 3 times daily, and discontinue use once symptoms improve, returning any remaining tablets to the study staff. Any treatment other than the trial intervention will be recorded, including timing and dose.

#### TA Group

Acupoint selection in the TA group is based on the points with the highest skin temperature in 8 specific lower limb regions (Figure 1). Our previous studies have indicated that, in patients with KOA, regional temperature increases occur in the lower limb acupoint areas as shown in Figure 1. These increases present a diffuse pattern resembling a “surface spread,” suggesting the presence of inflammatory reactions near the acupoint regions [20]. The areas with the highest temperatures are likely to correspond to locations of the most intense inflammatory responses. Therefore, these temperature-abnormal points will be selected as intervention acupoints in the TA group.

**Figure 1 figure1:**
[figure not shown]
The 8 regions on the lower limbs used for acupoint selection.

Acupoint selection will be performed using a system established by the research team, consisting of a custom-designed IRT image projection device (patent authorization number CN214748459U) and an auxiliary acupoint selection software system (patent authorization number CN114582489B). This system can project infrared images onto the body surface in real time (Figures 2A and 2B), monitor temperature extremes within the region, and visually present the data (Figure 2C).

**Figure 2 figure2:**
[figure not shown]
Infrared thermographic projection system for acupoint selection. (A) Infrared thermographic projection device; (B) real-time infrared image projected onto the body surface; (C) skin temperature recognition system. The squares indicate the automatically identified points with the highest skin temperature within the region.

The parameters of the IRT device are as follows: (1) a resolution of 640×512, (2) a temperature sensitivity of 0.05 ℃, (3) a field of view of 33.5°×26.9°, and (4) manufactured by Airui Optoelectronics Technology Co Ltd. The projector parameters are as follows: (1) a luminance of 1400 ANSI lumens, (2) a lens resolution of 1920×1080 (4K resolution), (3) the HK-610 model, and (4) an IRT image projection distance of 1 to 2 meters.

The background filtering method adopted is a bimodal filter. This method iteratively and statistically analyzes the 2D data of the image, calculates the distribution frequency curve for any temperature value, and applies a Gaussian smoothing filter. The image filtering threshold is automatically determined by locating the 2 peaks of the distribution curve, thereby filtering the raw image data and retaining only the target region of interest for the study. The maximum regional temperature value is calculated using an improved maximum value method.

Participants in the TA group will undergo IRT inspection before the first intervention session to determine the initial intervention points. Thereafter, IRT inspection will be repeated before the first session of each subsequent treatment week to update the acupoints accordingly. Therapists will record the treatment sites using photographs to ensure consistency within each treatment cycle.

#### CA Group

The CA group acupoint selection adopts a previously validated acupuncture intervention protocol [3]. It includes 5 fixed acupoints as follows: Dubi (ST35), Neixiyan (EX-LE5), Ququan (LR8), Xiyangguan (GB33), and an Ashi point (the point at which the patient experiences the most pain). Additionally, 3 optional acupoints will be selected based on the acupuncturist’s diagnosis from a pool of 22 possible acupoints. Detailed acupoint selection information is provided in Table S1 in Multimedia Appendix 2.

Participants in the CA group will undergo IRT inspection before the first intervention session each week, consistent with the procedure used in the TA group. However, these assessments will be intended solely for blinding purposes and will not inform the selection of acupuncture points.

### Outcomes

#### Primary Outcome

The primary outcome will be feasibility. Feasibility will be assessed throughout the trial period, including recruitment rate, retention rate, intervention adherence, and outcome assessment. A traffic light system will be used to evaluate feasibility (Table 1). Outcomes exceeding the upper threshold will be considered feasible; those falling between the upper and lower thresholds will be interpreted as having limited feasibility, and protocol modifications for each outcome will be considered in future studies to enhance feasibility to an acceptable level. If any outcome falls below the lower threshold, the trial will be considered infeasible. In such cases, the results will primarily be used to analyze the reasons for trial failure.

**Table 1 table1:** Feasibility assessment using a traffic light system.

Dimension	Lower threshold (%)	Upper threshold (%)
Recruitment rate	30	60
Retention rate^a^	70	80
Intervention completion rate^b^	70	90
**Outcome completion rate**		
VAS^c^ score	60	70
WOMAC^d^ function	60	70
Credibility and expectancy questionnaire	60	70
Skin temperature	60	70

^a^Including follow-up.

^b^Defined as completing at least 80% (10 sessions) of the intervention with no major protocol deviations.

^c^VAS: visual analog scale.

^d^WOMAC: Western Ontario and McMaster Universities Osteoarthritis Index.

#### Secondary Outcomes

##### Pain

Knee pain will be assessed using the VAS, a 100-mm scale in which one end represents “no pain” and the other represents “the worst pain imaginable” [26]. The VAS will be assessed at baseline and at weeks 2, 4, 8, and 12.

##### Function

Functional impairment will be evaluated using the Western Ontario and McMaster Universities Osteoarthritis Index (WOMAC) function subscale [27], which consists of 17 items rated on a 0 to 4 scale, with total scores ranging from 0 to 68. Higher scores indicate worse knee function. Assessments will be conducted at baseline and at weeks 2, 4, 8, and 12.

##### Expectancy

Expectancy will be measured using the credibility and expectancy questionnaire [28], which consists of 6 items. The first 3 items assess the credibility of the intervention, and the remaining 3 assess participants’ expectancy regarding the subjective effect. The questionnaire will be administered within 5 minutes after the first treatment session. Standardized scoring will be applied by adjusting each item score to have a mean of 0 and an SD of 1. The credibility score will be calculated as the sum of the standardized scores of the first 3 items, and the expectancy score, as the sum of the last 3 items.

##### Skin Temperature

Skin temperature at acupoints on the lower limb region will be measured using a portable medical IRT device. The measurement method will be the same as that used in our previous study [29] (Multimedia Appendix 2).

##### Safety

The safety of both interventions will be evaluated based on adverse events. Any adverse events will be documented within 24 hours of occurrence, and their relationship to the intervention will be determined by the research team. When necessary, the researcher responsible for maintaining the randomization sequence will perform unblinding. Serious adverse events will be referred to the principal investigator for further evaluation and management. Common adverse events related to acupuncture include pain, local hematoma, infection, and dizziness.

Feasibility, skin temperature, and safety outcomes will be assessed and documented by investigators. For participant-reported outcomes, investigators will first provide standardized explanations of questionnaire items, after which participants will complete the questionnaires independently, with minimal interaction to reduce potential influence. During the follow-up period, the questionnaire assessments will be conducted by telephone to improve retention.

### Sample Size

As this is a pilot study without previous evidence to estimate the difference between the current two groups, we selected a sample size of 30 participants per group based on the CI upper limit method [30]. Simulation studies suggest that this sample size provides stable estimates of variability, resulting in an 80% to 90% likelihood that a subsequent definitive trial will reach adequate power [31]. Assessment of treatment effects will be exploratory and intended to inform a future confirmatory trial, with CI bounds used because point estimates have limited precision in small samples [32]. In total, 60 patients will be recruited.

### Statistical Analysis

All statistical analyses will be performed using SPSS (version 20.0; IBM Corp). Multiple imputation will be used to address missing outcome data, with each missing value imputed 5 times and the mean of these imputations used for analysis. The intention-to-treat dataset will be used as the primary dataset. Feasibility outcomes will be primarily reported as observed proportions. The 95% CIs for feasibility outcomes will be calculated using Wilson score intervals and presented as a sensitivity analysis. Between-group differences in VAS scores, the WOMAC functional subscale, and credibility and expectancy scores will be assessed using either 2-tailed independent-sample *t* tests or Mann-Whitney *U* tests, as appropriate. Linear regression analyses will be conducted to examine the associations between within-group changes in VAS scores and skin temperature and their corresponding baseline values. Assessment of treatment effects will be exploratory. Results from the VAS and WOMAC will be used to estimate the effect size range for calculating the sample size of a definitive trial. Effect size will be quantified using Cohen *d*, with values of approximately 0.2, 0.5, and 0.8 representing small, medium, and large effects, respectively. All statistical tests will be 2-sided, with a significance level set at *P*=.05.

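### Averaging the 5 imputed values before analysis is single imputation: for outcomes with missing data it understates the SD and discards the imputation uncertainty that the definitive trial's planning needs

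*Protocol article*

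**What the plan says.** The Statistical Analysis section opens its treatment of missing data with the statement "Multiple imputation will be used to address missing outcome data". It then describes how the imputations enter the analysis: "with each missing value imputed 5 times and the mean of these imputations used for analysis". It does not mention analysing the five datasets separately or pooling their results. Group comparisons of VAS, WOMAC function and the credibility/expectancy scores "will be assessed using either 2-tailed independent-sample *t* tests or Mann-Whitney *U* tests, as appropriate", and "All statistical tests will be 2-sided, with a significance level set at *P*=.05". Linear regressions on change in VAS and skin temperature are also planned. The VAS and WOMAC results, expressed as Cohen d, are to supply the effect-size range for the definitive trial.

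The Sample Size section rests on the same quantities: "we selected a sample size of 30 participants per group based on the CI upper limit method", and "Simulation studies suggest that this sample size provides stable estimates of variability". It adds that CI bounds will be relied on because point estimates from a small trial are imprecise.

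Feasibility, the primary outcome, is reported as observed proportions with Wilson intervals. Treatment effects are called exploratory in both sections.

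**The concern.** Multiple imputation is valid because each completed dataset is analysed on its own, and the spread of the five answers is added to the standard error. Averaging the values first removes that spread. Each gap is then filled with something close to its predicted mean, so the completed data vary too little. The t test also treats all 60 values as observed and keeps 58 degrees of freedom.

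This matters because a pilot's SD and effect-size interval are what it hands to the next trial. If the SD is low and the interval too narrow, the reliance on CI bounds promised in the Sample Size section is weakened where it is needed. The sentence fixes a method explicitly, so this is not detail left to a separate analysis plan.

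**Working it through.** **Inputs from the article.** 30 per arm, 1:1; 5 imputations; two-sided 0.05; t or Mann-Whitney test. The article forecasts no missing share. Table 1 gives a range: retention thresholds of 70% and 80%, and VAS/WOMAC completion rated feasible above 70%. I take 20% and 30% missing, with 10% as an optimistic case.

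**Assumptions.** Baseline/follow-up correlation ρ of 0.3, 0.5 or 0.7; data missing completely at random; normal-regression imputation on baseline and arm; true SD 1.

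**Plan's own figure.** The article gives no SD, effect size, confidence level or target power behind 30 per group, so that number cannot be re-derived. This point does not depend on it.

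**Step 1: SD by formula.** A single draw carries residual variance 1 − ρ². The mean of 5 draws carries (1 − ρ²)/5, so four fifths is lost. With missing share p:

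Var ≈ 1 − p(1 − ρ²)(4/5)

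- p = 0.2, ρ = 0.3: 1 − 0.2 × 0.91 × 0.8 = 0.854, SD 0.92
- p = 0.2, ρ = 0.7: 1 − 0.2 × 0.51 × 0.8 = 0.918, SD 0.96
- p = 0.3, ρ = 0.3: 1 − 0.3 × 0.91 × 0.8 = 0.782, SD 0.88
- p = 0.3, ρ = 0.7: 1 − 0.3 × 0.51 × 0.8 = 0.878, SD 0.94

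**Step 2: simulation.** 8,000 trials per setting with no true effect and arm in the imputation model. Ranges run over ρ from 0.7 to 0.3.

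| Missing | SD after averaging | Type I, t test | Type I, Mann-Whitney | Type I, Rubin pooling |
|---|---|---|---|---|
| 10% | 0.974–0.959 | 6.4–7.5% | 6.0–7.6% | 4.8–5.1% |
| 20% | 0.954–0.919 | 8.3–10.5% | 8.1–11.5% | 4.6–4.8% |
| 30% | 0.932–0.880 | 9.9–14.8% | 10.0–16.2% | 4.4–4.7% |

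The SDs agree with the formula.

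**Step 3: standard error at ρ = 0.5.** The plan would report SD × √(2/30). At 20% missing that is 0.934 × 0.258 = 0.241, against a true sampling SD of 0.288, so 16% too small (0.241/0.288 = 0.84). At 30% it is 0.233 against 0.305, so 24% too small. Rubin pooling reports 0.287 and 0.307.

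**Step 4: carry-over to the definitive trial.** Per-arm n = 2(1.96 + z)²/d², with z = 0.842 for 80% power. A low SD multiplies n by SD².

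- Correct SD, d = 0.5: 15.70/0.25 = 62.8, so 63
- SD 0.92: 62.8 × 0.846 = 53.1, so 54
- SD 0.88: 62.8 × 0.774 = 48.6, so 49

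At 90% power the figures are 85, 72 and 66. The true power of the smaller trials is Φ(0.5√(n/2) − 1.96): about 74% with 54 per arm and 70% with 49, against the intended 80%.

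**Step 5: arm left out of the imputation model (ρ = 0.5).** Type I error is 5.2% at 20% missing and 5.0% at 30%, and the SD is still low (0.93 and 0.90). Here the imputed values do not differ systematically by arm, so a true difference Δ shrinks to about (1 − p)Δ. Cohen d then falls to about 0.8/0.93 = 0.86 or 0.7/0.90 = 0.78 of its true value. The inflation of d in Step 4 therefore assumes that arm is in the model.

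**The case against.** The strongest reply concerns scope and weight, because nothing in the article corrects the sentence itself.

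- **Primary outcome.** Feasibility is not imputed, and no decision in the article turns on a VAS or WOMAC P value. This stands, and it limits severity.
- **Reach.** A reader might infer that every SE and SD in the trial is affected. The article does not support that. Feasibility proportions are observed, credibility/expectancy is collected within minutes of the first session, and baseline VAS is needed for eligibility. The defect bites on outcomes with gaps.
- **False positives.** A reader might also infer that inflation is certain. No imputation model is stated, and Step 5 shows that the inflation disappears without arm. Only the low SD and the lost imputation variance are common to both models.
- **Missing share.** Retention between 70% and 80% is only limited feasibility in Table 1, so 20–30% dropout would prompt consideration of protocol changes. Even so, VAS or WOMAC completion just above 70% is rated feasible on its own line. The range is tolerated, not forecast.
- **Better predictors.** Other time points could predict the missing value better than baseline alone. The ρ = 0.7 results show the effect getting smaller but not vanishing.
- **Sampling error.** With 58 df the SD has a 95% range of about ±1.96/√116 = ±18%, larger than the bias. But that error is random, while this one always points down. If CI bounds means an upper 80% limit on the SD (level assumed), the margin is about 9%. Then 0.919 × 1.09 = 1.00 and 0.880 × 1.09 = 0.96, so the bias uses up the margin.
- **Intended meaning.** The authors may have meant pooling five sets of results. If so, the wording still needs correcting.

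**Conclusion.** The stated rule is wrong as written: it is single imputation under the name of multiple imputation. For outcomes with missing values the SD is understated by about 5–8% at 20% missing and 7–12% at 30%, and the between-imputation variance is dropped.

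With arm in the imputation model, Cohen d is inflated, its CI is too narrow, a definitive trial sized from it tends to be too small (54 or 49 per arm against 63 in the example), and type I error is about 8–11% at 20% missing and 10–16% at 30%. With arm omitted, type I error stays near 5% but the SD remains low.

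These sizes rest on assumed correlations of 0.3–0.7, data missing completely at random, and missing shares read from Table 1. At 10% missing they are smaller. The documents do not support saying that the definitive trial would certainly be undersized, or that the pilot's main conclusion is at risk. Severity is moderate.

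**What to change.** Replace the sentence with:

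> Each imputed dataset will be analysed separately, with arm, baseline and the other time points in the imputation model, and mean differences, regression coefficients and their standard errors will be combined by Rubin's rules; imputed values will not be averaged.

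Alternatively, fit a likelihood-based repeated-measures model to the observed VAS and WOMAC data, without imputation.

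Two further points need wording:

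- Mann-Whitney tests give no estimate and SE to pool. Run them on observed data only, or replace them with the model-based estimate.
- Take the SD for Cohen d and the definitive trial from observed data or from the pooled within-imputation variance.

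Five imputations already held type I error at 4.4–5.1% here, so the number need not change for this reason.

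The cost is wider intervals. At ρ = 0.5 the SE ratio is 0.287/0.241 = 1.19 at 20% missing and 0.307/0.233 = 1.32 at 30%. At ρ = 0.3 it is 1.23 and 1.39, and at ρ = 0.7 it is 1.13 and 1.21. Typical widening is thus about 20% and 30–40%, less where prediction is strong. Patients and data collection do not change. With 30 of 60 enrolled by January 1, 2026 and follow-up expected to end by June 2026, the change should be recorded as an amendment before the data are analysed.

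### Regressing change in VAS and in skin temperature on its own baseline builds in a negative slope, so these within-group regressions should not be tested or interpreted

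*Protocol article*

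**What the plan says.** The Statistical Analysis section of the protocol article plans linear regressions "to examine the associations between within-group changes in VAS scores and skin temperature and their corresponding baseline values". Two outcomes are named, VAS pain and skin temperature; the WOMAC function subscale is not. The same section adds: "All statistical tests will be 2-sided, with a significance level set at" .05. It labels the assessment of treatment effects exploratory.

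Two other places matter. Under Sample Size, "we selected a sample size of 30 participants per group based on the CI upper limit method". Under Participants, one inclusion criterion is "having a score ≥40 mm in the visual analog scale (VAS) [26] during the past week", so patients are selected on high pain at entry.

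**The concern.** If each change is regressed on its own baseline, the baseline measurement appears in the response with a minus sign and again as the predictor. A patient whose baseline reading happened to be high tends to show a fall, and one whose reading happened to be low tends to show a rise. A negative slope then arises from measurement error and ordinary within-person fluctuation alone (mathematical coupling and regression to the mean).

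Fitting the regression within each arm gives up the one feature of the design that removes this artefact, because regression to the mean acts alike in both randomised arms. The risk is that the pilot reports, with small P values, that patients with more pain improved more and that hotter skin cooled more, when neither need be true.

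**Working it through.** **Inputs from the protocol article.** 30 patients per group (Sample Size; 2 × 30 = 60, as stated there); two-sided level .05 (Statistical Analysis); VAS entry floor of 40 mm (Participants). The article gives no result for these regressions, so there is no stated figure to reproduce.

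**Assumptions, since the article does not give them.** Baseline/follow-up correlation r of 0.5, 0.7 and 0.9; equal SDs at both times (s1 = s2); the same true change in every patient; for the floor, VAS before selection with mean 55 and SD 20, and the entry VAS serving as the baseline.

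**Step 1: expected slope.** With Y1 baseline and Y2 follow-up, cov(Y2 − Y1, Y1) = r·s1·s2 − s1². Dividing by s1²:

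slope = r(s2/s1) − 1, which is −(1 − r) when s1 = s2.

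The change then has variance 2s²(1 − r), so corr(change, baseline) = −√((1 − r)/2).

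**Step 2: chance of false significance, no floor, n = 30.** The Fisher z approximation is Φ(√27 × atanh|corr| − 1.96), with √27 = 5.196.

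- r = 0.5: atanh(0.500) = 0.549; 5.196 × 0.549 − 1.96 = 0.89; 81%.
- r = 0.7: atanh(0.387) = 0.408; 5.196 × 0.408 − 1.96 = 0.16; 56%.
- r = 0.9: atanh(0.224) = 0.228; 5.196 × 0.228 − 1.96 = −0.78; 22%.

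Simulation (10,000 replicates) agrees: 83%, 58% and 22%.

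**Step 3: adding the 40 mm floor (VAS only).** Selecting on baseline leaves the expected slope unchanged but narrows the spread of baseline, so the correlation and the rejection rate fall.

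| Assumed r | Expected slope | Corr., no floor | False significant negative slope, no floor | Simulated corr., floor | False significant negative slope, floor |
|---|---|---|---|---|---|
| 0.5 | −0.50 | −0.50 | 83% | −0.39 | 59% |
| 0.7 | −0.30 | −0.39 | 58% | −0.30 | 37% |
| 0.9 | −0.10 | −0.22 | 22% | −0.17 | 15% |

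The no-floor column fits skin temperature, for which no entry threshold is stated; the floor column fits VAS. Even at r = 0.95 with the floor, the rate is about 9%.

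**Step 4: four regressions together.** Two outcomes in two arms, treated as independent, give P(at least one) = 1 − (1 − p_VAS)²(1 − p_temp)². At r = 0.7 this is 1 − (1 − 0.371)²(1 − 0.583)² = 1 − 0.396 × 0.174 = 93%. At r = 0.5 and 0.9 the results are about 99% and 55%.

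**Step 5: dependence on equal SDs.** The expected slope reaches zero only if s2/s1 = 1/r, that is 2.0, 1.43 and 1.11 at r = 0.5, 0.7 and 0.9. A follow-up SD 0.8 times the baseline SD makes the slope steeper: −0.60, −0.44 and −0.28.

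**Step 6: does a between-arm contrast remove it?** With 30 against 30, the floor applied and no true relation, the arm-by-baseline interaction was rejected in 4.4%, 5.2% and 4.9% of 4,000 simulated trials at r = 0.5, 0.7 and 0.9, close to the nominal 5%. This was run with change as the response. Using follow-up instead adds 1 to the baseline coefficient in both arms, so the interaction estimate and its test are identical.

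**The case against.** **The sentence is ambiguous.** It could mean that VAS change is related to temperature change, with baselines in the model, and separate fits by arm are inferred from the reference to within-group changes. This partly stands. Own-baseline regression is the more natural reading of corresponding baseline values, but the other is possible and the fix allows for it. Pooling the arms without a contrast would not help: at n = 60 without the floor, the false-significance rates are 99%, 88% and 41%.

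**The analysis is exploratory and decides nothing.** This stands as to weight. The section uses the VAS and WOMAC results, not these regressions, for the effect-size range of the definitive trial. But an exploratory label does not make a built-in slope informative, and the .05 level applies to all tests.

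**The size depends on unknown quantities.** This also stands. With high r the problem shrinks, and a negative slope need not be significant in any one regression.

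**Stronger readings that the document does not support.** A reader might infer that the regressions would falsely show baseline temperature predicting pain relief, and so appear to vindicate thermally guided points. Own-baseline coupling does not cross outcomes, and the article draws no such conclusion. A reader might also infer that the result would steer patient selection in the definitive trial; nothing gives it that role. The absence of a stated between-arm test of skin temperature is detail that a condensed article may leave to the analysis plan. Regression to the mean in average VAS, from the entry floor, is expected equally in both arms and does not bias the planned between-group tests.

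**Conclusion.** The point holds for the two named outcomes, VAS and skin temperature, on the natural reading of the sentence. The planned slopes have a negative expectation with no real relation behind them, and the tests reject far more often than 5% across the assumed range of r from 0.5 to 0.9. The exact rates rest on the assumed r, on equal SDs and, for the VAS floor, on the assumed mean and SD. The direction of the bias does not depend on those values unless the follow-up SD is larger than the baseline SD by a factor of 1/r or more.

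The damage is confined to these regressions. A stated analysis would mislead if followed, so it is worth correcting, but it does not threaten the trial's main conclusions.

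**What to change.** Replace the sentence. State that within-group slopes of change on own baseline will be neither tested nor interpreted. If the role of baseline is of interest, pool both arms and regress follow-up VAS and, in a separate model, follow-up skin temperature on its baseline, arm and the arm-by-baseline interaction; report the interaction with its 95% CI as exploratory.

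If the intention was to relate VAS change to temperature change, say so and adjust for both baselines and arm.

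Regressing change on the mean of baseline and follow-up (Oldham's method) is not a clean substitute for VAS here. Without the floor it rejects in about 5% of null samples, but with the 40 mm floor it is biased upward and rejects in 28%, 20% and 10% at r = 0.5, 0.7 and 0.9.

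The cost is wording only, on the same data. The Results section reports 30 participants enrolled by January 1, 2026 and provides for documented amendments. The downside is that an interaction estimated from 60 patients will be imprecise, so its interval, not its P value, should carry the message.
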